### Randomization, allocation concealment, and blinding

Eligible individuals will be randomized in a 1:1:1 ratio to one of the treatment regimens and a blocked randomization protocol will be designed to allocate an equal number of individuals to each group. The randomization code will be created using a blocked randomization procedure in SAS 9.4 (SAS Institute Inc., Cary, NC, USA) by a statistician who is not involved in the study. The block size is nine. All parameters will be maintained by statistician. According to the protocol, the research assistants who do not participate in the storage or allocation of the investigational drug will pack and label the investigational drug. Each package contains all the dosages of the investigational drug needed for the whole study. The eligible patients will receive a subject ID in order and be assigned drug package. The participants and raters will be blind to treatment allocation. If serious AEs, overdose, or severe drug interactions occur, blindness will be broken by PI with an emergency envelope for the purpose of guiding follow-up treatment to the allocation.

### Data collection and management

After enrollment, medical histories are collected via the case report form (CRF). Depressive symptoms, anxiety symptoms, and cognitive and functional impairments are assessed via the standardized Chinese version of the HRSD17, MARDS, QIDS-SR16, GAD7, CGI, SDS, and Perceived Deficits Questionnaire 5-Item (PDQ-D5) scales, respectively. The measures, participants, methods, assessment times, and administrators of the data collection are listed in Fig. 2. The data collected from medical records, dedicated scale manuals, well-designed questionnaires, laboratory/ECG test reports, and procedure records are defined as source data, and the data are structured and transcribed into CRF. After being reviewed by a quality control group and the PI, CRFs will be transferred to the data manager. Basic formats and logic checks will be performed by the data manager. Questionable data will be marked and the investigator will be informed to answer and modify the data. The database will be locked and stored after all questionable data is modified. Backup files for the database will be required to prevent defects. All transmissions of files will be recorded with signatures and be preserved following the good clinical practice (GCP) guidelines.

**Fig. 2 Fig2:**
[figure not shown]
Schedule of enrolment, intervention, and assessments (Standard Protocol Items: Recommendations for Interventional Trials (SPIRIT) diagram)

The research team includes qualified research staff authorized by the principle investigator ahead of any activity, investigators, independent raters, research nurses, and clinical research associate. The raters are continuously trained and tested by two senior raters and the inter-reliability of the primary outcome measure (HRSD17) is audited for each rater.

### Statistical analysis

All collected data will be analyzed using the SAS Statistical Package (version 9.4; (SAS Institute Inc., Cary, NC, USA). The sample characteristics will be compared using chi-square tests for categorical variables, with Fisher’s Z transformation when needed, and t-tests for normal quantitative variables or the Mann–Whitney U test for non-normal quantitative variables.

Efficacy analyses will be based on an intent-to-treat approach, corresponding to the full-analysis set (FAS), comprising all patients assigned to any treatment group and who have a valid baseline assessment of the primary efficacy outcome variables (HRSD17 total scores). Kaplan–Meier survival analyses will be used to calculate the estimated time from the baseline to early improvement. The Cox proportional hazards regression model will be applied to compare the estimated time to early improvement between the three groups, while controlling for covariates such as age, sex, and duration of illness. Secondary analyses will be performed to assess changes from baseline to each visit in terms of HRSD17, YMRS, CGI, and SDS total scores, using a mixed model of repeated measures (FAS, Mixed-Effect Model Repeated Measure model), with treatment as the fixed factor and baseline scores and age as covariates. A *P* value < 0.05 is considered as statistically significant. The statistical analysis protocol is validated before the interim analysis.

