Due to the lack of a known effective dose of intramuscular scopolamine in previous studies, we designed a dose-finding study using a scopolamine dose range that was previously associated with cognitive effects but without toxic effects such as delirium. In reference to the static drops in scopolamine antidepressant effective doses and to the recommended dose range of scopolamine injection specification, we chose a high-dose group (0.6 mg/day) and a low-dose group (0.3 mg/day). To ensure that the drug clearance was complete before the next injection, we designed the trial protocol to include morning and afternoon intramuscular injections each time; the treatment interval was 6 h.

Most of the trials were crossover studies and only used a single intravenous injection, limiting the generalizability of the findings. Previous studies have shown a rapid antidepressant effect of scopolamine; therefore, we added antidepressant treatment to see if scopolamine could accelerate the onset of antidepressant drugs. Our team’s research showed that single-dose intravenous ketamine augmentation by escitalopram was safe and effective in the treatment of severe MDD, showing the promise of speeding up early oral antidepressant efficacy [16]. To date, the effects of add-on scopolamine on currently available antidepressants have not been examined and it remains unknown whether concurrent initiation or oral antidepressant treatment with intramuscular scopolamine may increase antidepressant efficacy. Taking into account that the antidepressant effect of scopolamine is fast but not sustained, the focus of our study is on how to use scopolamine’s antidepressant effect to help patients with depression symptoms improve in the early stage. Therefore, we aimed to determine the antidepressant effects and safety of low-dose or high-dose single intramuscular scopolamine infusions, which were combined with escitalopram initiation in MDD.

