## Objectives

This study is designed to verify whether the augmentation of intramuscular scopolamine may accelerate the efficacy of antidepressant treatment.

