### Sample size

According to the published research and clinical expectations, we estimated the median time from the baseline to early improvement (at least a 20% reduction of HRSD17 score) of scopolamine plus escitalopram is 6.4 days and the four-week remission rate is 92.3%. The median time from the baseline to early improvement of placebo plus escitalopram treatments is 26.5 days and the four-week remission rate is 57.1%. Considering the time to early improvement, which is fitted to an exponential distribution, and assuming a power of 80% with a two-sided significance of 0.01, a minimal sample size of 54 was calculated using survival (time to event) modules. A common method for testing the proportional hazards assumption is to include a time interaction term to determine if the hazard ratio changes over time, since time is often the culprit behind non-proportionality of the hazards. Evidence that the group*time interaction term is not zero is evidence against proportional hazards. Assuming an attrition of 10%, at least 66 participants are planned.

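### The trial is sized on one scopolamine-versus-placebo contrast, but the Cox analysis compares three groups at 0.05 with no deciding contrast, test order or adjustment

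*Protocol article*

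**What the plan says.** All references are to the protocol article.

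- **Objectives.** The aim is to "verify whether the augmentation of intramuscular scopolamine may accelerate the efficacy of antidepressant treatment". No dose or contrast is named.
- **Background.** The authors write that "we designed a dose-finding study using a scopolamine dose range". There are two active arms, high and low, and one saline arm.
- **Sample size.** The median time to early improvement "of scopolamine plus escitalopram is 6.4 days and the four-week remission rate is 92.3"%. This is a single active figure with no dose attached. For the control arm, "The median time from the baseline to early improvement of placebo plus escitalopram treatments is 26.5 days". The calculation uses an exponential model, "assuming a power of 80% with a two-sided significance of 0.01", and gives 54 before attrition and 66 planned.
- **Statistical analysis.** "The Cox proportional hazards regression model will be applied to compare the estimated time to early improvement between the three groups", with covariates. A P "value < 0.05 is considered as statistically significant". No reference arm, contrast, order of tests or adjustment for several arms is given. The O'Brien-Fleming method under Monitoring deals with the interim look, not with the number of arms.

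The Cox analysis is not labelled primary. That it is the main test is an inference: the sizing uses the same time-to-event endpoint, and the analyses listed after it are called secondary.

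**The concern.** The sizing has two groups and the analysis sentence has three. Four tests fit the text: high dose versus placebo, low dose versus placebo, pooled scopolamine versus placebo, and a global 2-df test across the arms. Each answers a different question. The global test has no direction and also reacts to a difference between the two doses, so on its own it does not answer the stated objective. Two separate dose-versus-placebo tests do answer it, but at 0.05 each they exceed the nominal error rate. Where the doses differ in effect, the same data can be significant under one choice and not under another. The issue remains whichever single significance level is used.

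**Working it through.** **1. Reproducing the 54.** Inputs from the Sample size section: medians 6.4 and 26.5 days, exponential times, two-sided 0.01, 80% power. Follow-up is 28 days.

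- Hazard ratio: 26.5/6.4 = 4.14; ln(4.14) = 1.421.
- 28-day event probabilities: active 1 − 2^(−28/6.4) = 0.952; placebo 1 − 2^(−28/26.5) = 0.519.
- n per arm = (z_0.995 + z_0.80)² × (1/p1 + 1/p0) / ln(HR)² = 11.68 × (1.051 + 1.926) / 2.019 = 17.2, so 18.
- 3 × 18 = 54, the stated figure.

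Pooled scopolamine (2:1) versus placebo by the same formula: 11.68 × (0.525 + 1.926) / 2.019 = 14.2, so 15 per arm and 45 in total. The 54 therefore fits one dose arm against placebo, repeated over three equal arms. It does not show which dose.

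**2. Error rates under the two main readings (two-sided 0.05, no true effect).**

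- Global 2-df test: it rejects in 5.0% of trials. In 2.9 of those 5.0 points neither dose is significantly faster than placebo. In about 1.7 points placebo is the fastest arm.
- Two unadjusted dose-versus-placebo tests: they share the placebo arm, so their correlation is 0.5. The chance that at least one is significant in either direction is 9.1%.

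**3. Does the choice change significance?** Arm log-hazards were simulated as normal with variance 1/(n × event probability), 28-day follow-up and a placebo median of 26.5 days. The pooled test weights the doses by information. Contrasts count as successes only when they favour scopolamine. The level is 0.05 with 18 per arm. The hazard ratios in the first, second and fourth rows are assumed in whole or in part; only the third row uses the protocol's stated effect for both doses.

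| HR high / HR low | High | Low | Pooled | 2-df | All four not in agreement |
|---|---|---|---|---|---|
| 2.5 / 1.5 | 60% | 15% | 44% | 51% | 51% |
| 4.14 / 2.03 (half the log-HR) | 94% | 39% | 84% | 90% | 56% |
| 4.14 / 4.14 | 94% | 94% | 97% | 94% | 9% |
| 4.14 / 1 (low dose inert) | 94% | 2.5% | 68% | 97.5% | 96% |

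- High versus placebo succeeds while pooled fails in 17% of trials in the first row and 10% in the second.
- With the low-dose test left out, high, pooled and 2-df disagree in 27% and 13% in those two rows.
- With both doses at 4.14, disagreement among all four is 9% at 18 per arm and 5% at the planned 22 per arm.

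**4. One illustrative data set.** With 22 per arm and first improvements at days 4, 7, 14 and 28 of 2/2/3/5 (placebo), 2/3/4/4 (low) and 6/5/5/4 (high), an unadjusted Cox model gives a global p = 0.003, high versus placebo p = 0.003, low versus placebo p = 0.70 and pooled versus placebo p = 0.071.

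**5. Can 66 patients carry a named choice?** At 22 per arm and the design effect, the closed formula gives power of 90% for one contrast at 0.01, 97% for one contrast at 0.05, and 95% per contrast for two contrasts at 0.025 each.

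**The case against.** The strongest reply is that this is one sentence of a condensed article. The same section refers to a separate analysis protocol, which could name the reference arm and the order of tests. Sizing a three-arm trial on one pairwise effect is common, and a Cox model with a three-level factor yields exactly those pairwise hazard ratios. No global test is mentioned. This much stands: the article does not show that the contrast would be chosen after the data are seen, and the 2-df test is only one reading. What remains is that the text as written pairs a one-contrast sizing with a three-group comparison at 0.05, and either main reading has a defect that can be quantified.

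Three stronger inferences are tempting and are not supported.

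- **That the candidate tests give opposite verdicts, in about half of trials.** The disagreement is significant versus not significant, never faster versus slower. Most of the 51% to 56% comes from the weaker low dose missing significance, which is a legitimate result in a dose-finding trial. It also rests on dose effects that the protocol does not state.
- **That the global test is always weaker than the high-dose contrast.** If the low dose is inert it is stronger: about 97% against 94%.
- **That the sizing singles out high dose versus placebo.** No dose is named, and 18 per arm fits either one.

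The sizing level of 0.01 might be a tacit allowance for several contrasts (3 × 0.01 = 0.03). No section says so, and the analysis section decides at 0.05.

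**Conclusion.** The concern holds in a limited form. The sizing is for one dose-versus-placebo contrast, while the analysis compares three groups at 0.05 and fixes no contrast, order or adjustment. A global test leaves the objective unanswered in the sense of step 2, and two unadjusted pairwise tests carry about 9% two-sided familywise error. Neither figure depends on assumed dose effects.

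How often the choice alters significance does depend on them. It is about 10% to 17% for high versus pooled in the two assumed graded scenarios at 18 per arm. Under the only effect the protocol states, applied to both doses, disagreement is about 5% to 9%. These figures rest on exponential times and a normal approximation. The planned sample can support any of the usual choices under the design effect, so what is lacking is the choice, not patients. It should be corrected, but it does not undermine the design.

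**What to change.** In Statistical analysis, replace the three-group comparison with named dose-versus-placebo contrasts from the three-arm Cox model, tested in a prespecified order that controls the error rate. One example is high dose versus placebo first and low dose versus placebo only if the first is significant, with high versus low reported as an estimate and confidence interval only. Which contrast comes first is a design decision for the investigators. In Sample size, state that the number powers one dose-versus-placebo contrast, and use the same significance level in both sections.

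The change is to wording and needs no additional patients. The cost of the ordered test is that the second contrast, low dose versus placebo in this example, cannot be claimed if the first fails.

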### Interventions

Individuals are equally and randomly allocated to three treatment regimens groups that are different only for the first three days: (1) the high-dose group receives 0.3 mg of intramuscular scopolamine twice daily; (2) the low-dose group receives 0.3 mg of scopolamine in the morning and saline in the afternoon; and (3) the saline-controlled group is injected with intramuscular saline twice daily. After the first three days of add-on injections, the participants receive monotherapy with a fixed dose of oral escitalopram for the remaining 25 days. Injections are administered at 09:00 and 15:00 by the research nurse.

All the individuals stay in the emergency wards during the first three days and receive clinical visits on the 4th, 7th, 14th, and 28th day from the first injection.

See “Fig. 1 Study flow chart” for a detailed overview of the research procedure.

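### Early improvement can be seen only at a few visits, so the Cox analysis needs a stated method for ties, and its single hazard ratio to day 28 needs pre-specified supportive summaries

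*Protocol article*

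**What the plan says.** All references are to the protocol article.

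- Statistical analysis: Kaplan-Meier estimates of time to early improvement, then "The Cox proportional hazards regression model will be applied to compare the estimated time to early improvement between the three groups", adjusted for covariates such as age, sex and duration of illness. The section does not mention tied event times or interval censoring.
- Interventions: after three days on the ward, patients "receive clinical visits on the 4th, 7th, 14th, and 28th day from the first injection". Patients are "allocated to three treatment regimens groups that are different only for the first three days"; all then continue on escitalopram alone.
- Background: "the antidepressant effect of scopolamine is fast but not sustained", and the stated focus is improvement in the early stage.
- Sample size: medians of 6.4 days (scopolamine plus escitalopram) and 26.5 days (placebo plus escitalopram), under an exponential model: "Considering the time to early improvement, which is fitted to an exponential distribution". The same section adds: "A common method for testing the proportional hazards assumption is to include a time interaction term". It does not say what follows if that test indicates non-proportional hazards.
- Data collection and management: assessment times are listed in Fig. 2, which is not shown.

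**The concern.** There are two separate issues.

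**Timing of the event.** A 20% fall in HRSD17 is known only to have happened between two ratings, and the last gap between stated visits is 14 days. Events therefore gather on a handful of dates. A Cox model for continuous time then depends on how ties are handled, and a Kaplan-Meier median can only equal a rating day.

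**Shape of the effect.** The sample size and the model both assume one hazard ratio that holds to day 28. The rationale is a short add-on course whose effect comes early and fades. If that is right, the hazard ratio would fall over time and a single estimate would average an early difference with a later period of little or none. The only safeguard is the group-by-time test.

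At stake are the size of the headline hazard ratio, the reported medians and, in some settings, a good deal of power.

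**Working it through.** **1. The plan's own figure.** Inputs from Sample size: medians 6.4 and 26.5 days, exponential times, power 80%, two-sided 0.01, follow-up 28 days.

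- Hazards: ln 2/6.4 = 0.1083 per day; ln 2/26.5 = 0.0262 per day. Hazard ratio = 26.5/6.4 = 4.14, ln = 1.421.
- Improved by day 28: 1 − exp(−28 ln 2/6.4) = 0.952; 1 − exp(−28 ln 2/26.5) = 0.519.
- n per arm = (2.576 + 0.842)² × (1/0.952 + 1/0.519) / 1.421² = 11.68 × 2.977 / 2.019 = 17.2, so 18 per arm and 54 in three arms. The stated 54 is reproduced, and it rests on a hazard ratio of 4.14 held for 28 days.

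**2. How heavy the ties are.** The probability of first being seen improved at each of the four visits, under the planning hazards:

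| Arm | Day 4 | Day 7 | Day 14 | Day 28 |
|---|---|---|---|---|
| Scopolamine | 0.352 | 0.180 | 0.249 | 0.171 |
| Placebo | 0.099 | 0.068 | 0.139 | 0.213 |

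With 18 per arm, one active arm and placebo give 18 × (0.952 + 0.519) = 26.5 expected events on four dates, about 8.1, 4.5, 7.0 and 6.9.

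**3. Medians.** Cumulative improvement on scopolamine is 0.352 at day 4 and 0.531 at day 7, so the median reads 7. On placebo it is 0.306 at day 14 and 0.519 at day 28, so it reads 28.

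**4. Effect of tie handling.** Simulated trials, one active arm against placebo, unadjusted, constant hazard ratio 4.14, two-sided 0.01 (2,000 to 3,000 trials per setting; 500 for the grouped-time model):

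| Analysis | Power, 18 per arm | Median HR, 18 per arm | Power, 22 per arm |
|---|---|---|---|
| Cox, exact times | 0.84 | 4.24 | 0.92 |
| Cox at visit days, Efron | 0.81 | 4.01 | 0.91 |
| Cox at visit days, Breslow | 0.62 | 3.18 | 0.75 |
| Grouped-time, complementary log-log | 0.84 | 4.57 | 0.93 |

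The simulation error of a power near 0.81 from 2,000 trials is √(0.81 × 0.19/2000) ≈ 0.009. A second simulation at 18 per arm gave 0.80 (HR 4.07) with Efron and 0.63 (HR 3.23) with Breslow. Type I error on the visit days with Efron ties was 0.006 at the 0.01 level and 0.043 at 0.05.

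**5. Effect of a fading hazard ratio.** The documents do not give the duration of effect, so it is a range: hazard ratio 4.14 to day c and 1 afterwards. Improvement by day 28 on active treatment is 1 − exp(−0.1083c − 0.0262(28 − c)); for c = 7 this is 1 − exp(−1.307) = 0.729. Power is for Cox with Efron ties at the visit days, 22 per arm; ranges span repeat simulations.

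| Effect ends on day | Improved by day 28 (placebo 0.519) | Power at 0.01 | Power at 0.05 |
|---|---|---|---|
| 3 | 0.624 | 0.04–0.05 | 0.16 |
| 4 | 0.654 | 0.07 | 0.21–0.22 |
| 7 | 0.729 | 0.23–0.26 | 0.47–0.48 |
| 14 | 0.848 | 0.65 | 0.86 |
| 17 | 0.881 | 0.73–0.76 | 0.89–0.90 |
| 28 | 0.952 | 0.90 | 0.98 |

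Both levels are shown because the Sample size section plans at 0.01 and the Statistical analysis section tests at 0.05. Day 17 is the third injection day plus the two weeks of benefit that Background reports for earlier infusion studies.

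**6. Model or smaller effect?** With the effect ending on day 7 (22 per arm, 0.01), Cox has power 0.23, a Gehan-weighted test 0.35 and a comparison of day-7 proportions 0.50. All are far below the 0.90 available when the effect lasts. If the effect does last to day 28, day-7 proportions have power of only 0.52 against 0.90 for Cox.

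**7. The group-by-time check.** A test of early (to day 7) against late hazard ratio at 0.05, with 22 per arm, detects the change in about 20% of trials if the effect ends on day 4 and 33% if it ends on day 7.

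**The case against.** The strongest reply is that this is largely detail for an analysis plan. The article nowhere says that visit dates are treated as exact times, and a rule for ties may well stand in the separate statistical analysis document it mentions. All arms share the same visits, so with Efron ties the visit grid costs at most about 3 points of power and does not inflate type I error. A reader might infer that, because SAS is named, Breslow ties will be used; the article does not say so. Fig. 2 may also add ratings on the ward in the first three days, though these would not close the gap between days 14 and 28. All of this stands, and it limits the first issue to a conditional one.

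On the second issue, a reader might infer that arms treated differently for three days can differ in hazard for only three days, so that the Cox model throws away most of the power. The documents do not support that. Background reports benefit for two weeks after the last infusion, and the four-week planning rates (92.3% and 57.1%, labelled remission) keep the arms far apart. A benefit that is not sustained is also not the same as a hazard ratio for first improvement that returns to 1. Where power does collapse, step 6 shows that most of the loss comes from the smaller effect. The article also plans analyses of score changes at each visit, where an early difference could appear.

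What remains is that the Cox model and the sparse visits are both stated in this document, the gap between tie methods is large, and the group-by-time check leads to no action.

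**Conclusion.** The point holds in a limited form and should be acted on.

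- **Ties.** The analysis will be heavily tied, and medians can be read only to a rating day. Serious harm follows only if ties are handled by Breslow's approximation, which is an assumption: the hazard ratio is then about 3.2 instead of 4.14, and power about 0.62 instead of 0.84 (18 per arm, 0.01). It would be wrong to say that the visit grid by itself biases the result materially.
- **Single hazard ratio.** It fits poorly with the stated rationale, but non-proportional hazards are plausible, not established. Power at 22 per arm and 0.01 runs from 0.23–0.26 (effect to day 7) through 0.65 (day 14) and 0.73–0.76 (day 17) to 0.90 (day 28). A non-significant group-by-time test would give little reassurance. This supports pre-specified descriptive summaries; it does not justify replacing the primary test.

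The figures rest on the planning hazards, the four stated visits, unadjusted comparison of one active arm with placebo and an assumed range for the duration of effect.

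**What to change.** 1. Keep one primary treatment test. Fit it as a Cox model with Efron or exact ties, or as a grouped-time proportional hazards model: binary regression with a complementary log-log link, one intercept per visit, treatment and the planned covariates. Both target the same hazard ratio. In the small samples simulated here the grouped-time estimate ran somewhat high (4.57) and the Efron estimate slightly low (4.01), so changing the tie option alone is enough.
2. Report median times as the visit interval in which the median falls, for example between days 14 and 28.
3. Whatever the P value of the group-by-time term, pre-specify as supportive, not additional primary, results: the cumulative proportion improved at each visit with differences from placebo, and the difference in restricted mean time to improvement up to day 28.
4. State that the group-by-time term will be reported as description and will not decide which analysis is primary.

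The cost is a few lines of analysis text and code and a little more reporting. No new data are needed. The choices should be fixed before unblinding.

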#### Inclusion criteria

Aged 18–45 years;diagnosis of MDD according to the Diagnostic and Statistical Manual of Mental Disorders, Fourth Edition (DSM-IV) criteria;a total score of the 17-Item Hamilton Rating Scale for Depression (HRSD17) ≥ 20;duration of the index episode is ≥ 4 weeks.

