### Outcomes

The primary outcome for this study is improvement of the HRSD17 score from the baseline to 28 days (at least a 20% reduction). Secondary outcomes are response rate (a 50% decrease in HRSD17 score from baseline), remission rate (HRSD17 score ≤ 7), changes in HRSD17, MADRS, Quick Inventory of Depressive Symptomatology Self Report 16-Item (QIDS-SR16), Generalized Anxiety Disorder 7-Item (GAD-7), Young Mania Rating Scale (YMRS), and Clinical Global Impression (CGI) Scale scores throughout the trial.

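### The primary Cox model does not name baseline HRSD17 among its covariates; adding it costs almost nothing and may gain precision

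*Protocol article*

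**What the plan says.** Under Statistical analysis, the protocol article compares time to early improvement between the three groups with a Cox model, "while controlling for covariates such as age, sex, and duration of illness". The list is given by example, and baseline HRSD17 is not among the examples.

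Four other statements bear on this:

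- Statistical analysis, full-analysis set: it is limited to randomized patients "who have a valid baseline assessment of the primary efficacy outcome variables (HRSD17 total scores", so the score is available for everyone analysed.
- Statistical analysis, secondary mixed model: it is fitted "with treatment as the fixed factor and baseline scores and age as covariates".
- Inclusion criteria: entry requires "a total score of the 17-Item Hamilton Rating Scale for Depression (HRSD17) ≥ 20".
- Outcomes: the primary outcome is "improvement of the HRSD17 score from the baseline to 28 days (at least a 20% reduction", so each patient's own baseline is the denominator of the event.

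The section on randomization describes 1:1:1 allocation in blocks of nine and states no stratification by severity.

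**The concern.** Baseline HRSD17 selects patients into the trial and sets the size of fall that counts as an event. A patient entering at 20 needs a drop of 4 points; one entering at 30 needs 6. The time to reach that fall may therefore depend on baseline, in a direction and to a degree that cannot be told in advance. Allocation is not said to be balanced on severity, so with about 22 patients per arm only the model can deal with a chance difference.

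What is at stake is precision. If baseline predicts the event, a Cox model without it gives a treatment effect pulled towards the null and lower power, and a severity imbalance in the realised sample carries into the estimated hazard ratio. The authors plan to use baseline scores in the secondary model, and the article gives no reason for not naming the score in the primary one.

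**Working it through.** **Inputs from the protocol article.** Medians of 6.4 and 26.5 days; "assuming a power of 80% with a two-sided significance of 0.01"; 66 patients, so 22 per arm; follow-up to day 28; P < 0.05 at analysis.

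**Assumed, not in the document.** The log-hazard effect of baseline HRSD17 per SD, taken from 0 to 0.7. Hazard ratios of 2.0 and 2.5 are illustrative smaller effects.

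**1. The plan's own figure.** Under exponential times:

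- HR = 26.5/6.4 = 4.14, and ln HR = 1.421.
- Event probability by day 28 is 1 − 2^(−28/6.4) = 0.952 on scopolamine and 1 − 2^(−28/26.5) = 0.519 on placebo.
- n per arm = (2.576 + 0.842)² × (1/0.952 + 1/0.519) / 1.421² = 17.2, rounded up to 18.
- Three arms give 54, the stated minimum. No covariate enters this calculation, so the point does not disturb it.

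**2. Size of chance imbalance.** With 22 per arm, the difference in mean baseline between two arms has standard error √(2/22) = 0.302 SD.

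- 95% limit: 1.96 × 0.302 = 0.59 SD. At 0.3 per SD the factor on the hazard ratio is exp(0.3 × 0.59) = 1.19; at 0.7 it is exp(0.7 × 0.59) = 1.51.
- Median absolute difference: 0.674 × 0.302 = 0.20 SD. The corresponding factors are about 1.06 and 1.15.

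**3. Power without and with baseline HRSD17.** Simulated Cox models for one pairwise comparison: 22 per arm, exponential times censored at day 28, a standard normal baseline, two-sided 0.05. There were 1,500 runs per setting (500 at HR 4.14), and Monte Carlo error is about 1 to 3 points.

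| Assumed effect per SD | HR 4.14 (planned) | HR 2.5 | HR 2.0 |
|---|---|---|---|
| 0 | 97% → 97% | 71% → 71% | 44% → 43% |
| 0.2 | 97% → 97% | 68% → 68% | 41% → 43% |
| 0.3 | 98% → 99% | 67% → 69% | 40% → 43% |
| 0.5 | 94% → 97% | 57% → 65% | 36% → 44% |
| 0.7 | 90% → 96% | 52% → 68% | 33% → 41% |

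Type I error without adjustment was 4% to 5% throughout. Where baseline has no effect, adding it changes power by no more than simulation noise.

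**4. Sensitivity to the significance level.** The sample size was planned at 0.01, not 0.05. At 0.01 and HR 4.14, with event times grouped to the visits on days 4, 7, 14 and 28, adjustment moves power from 87% to 89% at 0.3 per SD and from 70% to 87% at 0.7. The pattern is the same, with a larger gain where baseline is strongly prognostic.

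**The case against.** Several objections are fair.

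- **The list is illustrative.** A reader might infer that baseline HRSD17 is excluded from the primary model. The text does not say so; *such as* leaves room for it. This stands: the point is that the score is not named, not that it is ruled out.
- **Closing the list belongs to the analysis plan.** A reader might infer that covariates will be picked once results are known. The article says the statistical analysis protocol is validated before the interim analysis, and nothing shows that the choice stays open beyond that. This stands too, so the open wording is not a fault in itself.
- **Loss of power is not established.** The documents give no prognostic strength. A percentage endpoint already scales to each patient's baseline, and the entry threshold narrows the range, so the effect may be small. At HR 4.14 and 0.05, power without adjustment is still 90% under the strongest assumption. This stands as a limit on size.
- **Randomization keeps the comparison valid.** Chance imbalance is part of the sampling variation that the confidence interval reflects, and the typical factor (1.06–1.15) is well below that at the 95% limit. This is right: the issue is precision and the estimate in the sample at hand, not an invalid test.
- **The two models differ in kind.** Baseline adjustment is routine for change scores, so naming it only in the mixed model is no contradiction. Agreed.

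None of this gives a reason to leave the score out. Adjustment carried no material power cost in any setting examined.

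**Conclusion.** The point holds as a free improvement of low to moderate importance. The primary Cox model does not name the score that forms the denominator of its own event, although it is on hand for every analysed patient.

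The benefit is conditional. At 0.05 it is negligible at or below about 0.2–0.3 log-hazard per SD. At 0.5–0.7 it is about 3–6 power points at the planned hazard ratio of 4.14 and roughly 8–16 points at 2.0–2.5. At the planning level of 0.01 and HR 4.14 it ranges from about 2 points (at 0.3) to 17 points (at 0.7). These figures rest on the assumed prognostic effect, a normally distributed baseline, exponential times, no attrition, and one pairwise comparison without the other covariates.

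The documents do not support saying that the plan omits baseline by design, that it certainly loses power, that the test is biased, or that the sample size is wrong.

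**What to change.** In the analysis plan, before the interim analysis, define the primary Cox model as adjusting for baseline HRSD17 (continuous), age, sex and duration of illness. State this as the full list rather than as examples. If the authors prefer to leave baseline HRSD17 out, give the reason.

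The cost is one phrase and one degree of freedom, with no new data. The model already adjusts for patient characteristics, so its hazard ratio is already a conditional one; adding baseline does not change the kind of effect reported.
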